## Abstract

**Aims:**

There is a lack of data from randomized clinical trials comparing treatment outcomes between conduction system pacing (CSP) modalities and biventricular pacing (BVP) in symptomatic patients with refractory atrial fibrillation (AF) scheduled for atrioventricular node ablation (AVNA). The CONDUCT‐AF investigates whether CSP is non‐inferior to BVP in improving left ventricular ejection fraction (LVEF) and clinical outcomes in heart failure (HF) patients with symptomatic AF undergoing AVNA.

**Methods:**

This study is an investigator‐initiated, prospective, randomized, multicentre clinical trial conducted across 10 European centres, enrolling 82 patients with symptomatic AF, HF with reduced LVEF, and narrow QRS. Participants will be randomized 1:1 to CSP or BVP with subsequent AVNA and followed for at least 24 months. The primary endpoint is the change in LVEF after 6 months. Secondary endpoints will include time to the first occurrence of worsening HF or cardiovascular death and its individual components, total number of HF hospitalizations, change in quality of life, N‐terminal pro‐B‐type natriuretic peptide, 6‐min walk test distance, and safety outcomes.

**Conclusions:**

The CONDUCT‐AF trial will provide critical insights into the optimal pacing modality for patients with HF and refractory AF undergoing AVNA. Recruitment is expected to conclude in 2025, with the first study results anticipated in 2026.

## Introduction

### Atrial fibrillation in heart failure

Disorganized atrial activity during atrial fibrillation (AF) has many deleterious haemodynamic effects contributing to cardiac remodelling and induction of fibrosis.^1^, ^2^, ^3^ Early studies proved that irregularity and loss of atrial contribution to left ventricular (LV) filling decreased cardiac output (CO).^4^ Further exploration revealed that independent of rate, irregular ventricular rhythm disables cardiac contractility to adapt during beat‐to‐beat changes in ventricular filling. In addition, AF leads to insufficient coronary flow, molecular LV remodelling, and disrupted Ca^2+^ homeostasis, which eventually may induce contractile dysfunction.^3^, ^5^ In brief, deleterious haemodynamic effects of AF on cardiac function can be attributed to loss of atrial contraction, reduced CO, and irregular and often rapid heart rate.^2^, ^6^ Considering these facts, removing irregularity and fast ventricular response alone can increase CO and prevent long‐term deleterious effects of AF culminating in arrhythmia‐induced cardiomyopathy.

### Treatment strategies

Catheter ablation enables restoration of sinus rhythm and several studies have recently demonstrated its prognostic benefit.^7^, ^8^, ^9^ Therefore, current guidelines recommend CA as a first‐line treatment when arrhythmia‐induced cardiomyopathy is highly probable (class I, level of evidence B, European and US guidelines).^10^, ^11^ However, these benefits might be less distinct in patients with long‐standing, persistent AF in whom lower interventional success rates might be expected.^12^ Additionally, most trials do not specify ablation outcomes in persistent AF or elderly patients with more comorbidities in whom recurrences may be particularly problematic. Therefore, even though the guidelines recommend CA as a treatment of choice, alternative therapeutic strategies may be considered. Atrioventricular node ablation (AVNA) with permanent pacemaker implantation (pace and ablate strategy) is a feasible rate control option that offers more robust control of ventricular rate over medical therapy alone, as well as definitive rhythm regularization.^13^ A recent meta‐analysis compared the efficacy and safety endpoints among five major approaches for AF. Although CA performed best in reducing AF recurrence, the pace and ablate strategy showed superiority in reducing mortality and rehospitalization.^14^ Current 2024 European Society of Cardiology guidelines recommend AVNA in patients unresponsive or intolerant to intensive rate and rhythm control therapy, and not eligible for rhythm control by CA (class IIa, level of evidence B). The choice of pacing modality depends on patient characteristics and the presence of heart failure (HF).^10^

### Pacing modalities in the pace and ablate strategy

Right ventricular pacing (RVP) combined with AVNA has demonstrated its potential to effectively improve clinical outcomes.^15^ However, the beneficial effects of rate control and regularization after AVNA could be hampered by non‐physiological asynchronous contraction after RVP.^16^ Deleterious effects of RVP can be avoided with biventricular pacing (BVP). As demonstrated in the APAF‐CRT study, BVP combined with AVNA significantly reduced mortality, HF hospitalizations, and improved LV function.^17^, ^18^ However, the benefit was less distinct in symptomatic AF patients with moderately reduced left ventricular ejection fraction (LVEF) and narrow QRS. BVP circumvents the dyssynchrony induced by RVP but still induces abnormal epicardial activation that results in QRS prolongation and some extent of electrical and mechanical dyssynchrony.^3^, ^17^, ^19^

In recent years, conduction system pacing (CSP) modalities, including His bundle pacing (HBP) and left bundle branch area pacing (LBBAP), have evolved as a promising alternative allowing the most physiological activation of the myocardium. Retrospective studies demonstrated both the feasibility and advantages of HBP in echocardiographic outcomes and time to death or HF hospitalization compared to conventional RVP.^20^ Although the His bundle appears to be the ideal physiological pacing site, its proven feasibility alongside AVNA must be considered in light of some significant limitations. The implant technique is challenging and requires advanced implantation tools and longer procedural and fluoroscopic times. Low sensing values could engender atrial oversensing in pacemaker‐dependent patients. Moreover, higher pacing thresholds and their further rise after AVNA due to the proximity of the ablation site to the implanted HBP lead might be observed, necessitating a right ventricular (RV) backup lead and early battery replacement.^21^, ^22^ In contrast, LBBAP lead is implanted in the region of the left bundle in the septum, which has an adequate distance from the AVNA site. Therefore, this modality could minimize the risk of an increase in capture threshold after AVNA. Additionally, the pacing parameters of LBBAP were stable in long‐term follow‐up studies, precluding the need for back‐up pacing and early battery replacement. Therefore, compared to HBP, LBBAP may offer a more feasible physiological pacing option, especially in patients undergoing AVNA.^21^

Some observational studies have already shown superior symptomatic and echocardiographic improvement in symptomatic AF patients who underwent CSP, both HBP and LBBAP, compared to BVP after AVNA, especially in HF patients with narrow baseline QRS and reduced LVEF (<50%).^23^, ^24^ Therefore, it is reasonable to assume that CSP, in conjunction with AVNA, could represent a promising alternative to BVP in refractory AF patients. Nevertheless, the 2021 guidelines give BVP a class IIa recommendation for those with mildly reduced and a class I for those with reduced LVEF. In contrast, HBP is allowed as an alternative with class IIb, and recommendations for LBBAP remain to be formulated.^25^

### Study rationale and aim

Data from randomized clinical trials comparing treatment outcomes between CSP and BVP in combination with AVNA are lacking. The need for a comparison between both pacing modalities in the treatment of refractory symptomatic AF constituted the rationale for the CONDUCT‐AF study.

## Study design

CONDUCT‐AF is an investigator‐initiated, prospective, multicentre, randomized, single‐blinded, two‐arm clinical trial conducted in 10 European centres (ClinicalTrials.gov: NCT05467163). Eighty‐two patients with symptomatic AF, HF, and narrow QRS will be randomized in a 1:1 ratio to CSP or BVP with subsequent AVNA (*Graphical Abstract*) using a computer‐generated randomization sequence stratified by centre, gender, and LVEF below or above 35%.

The study will follow the Declaration of Helsinki, Good Clinical Practice, and the applicable local regulatory requirements. It was initiated after approval from the institutional review and ethics board at each centre. The authors, who are responsible for writing this paper and its final content, designed the protocol.

### Study population and enrolment

Patients with reduced LVEF (<50%), narrow intrinsic QRS (≤120 ms), initial N‐terminal pro‐B‐type natriuretic peptide (NT‐proBNP) >600 ng/L, and refractory symptomatic AF despite guideline‐directed medical therapy or failed catheter ablation are candidates for participation in this study. Detailed inclusion and exclusion criteria are presented in *Table* *1*. All patients will receive detailed clarification from local investigators and will provide their written informed consent before enrolment. A screening log with reasons for inclusion failure will be collected at each site.

**Table 1 ejhf70013-tbl-0001:** Inclusion and exclusion criteria in the study

Inclusion criteria	Exclusion criteria
Symptomatic permanent AF refractory to drug therapy or failed catheter ablation Left ventricular ejection fraction <50% Narrow intrinsic QRS ≤120 ms NT‐proBNP >600 ng/L Age between 18 and 85 years	Pre‐existing permanent PM, ICD or CRT device with >5% of paced beats (i.e. backup pacing) Life expectancy <12 months Severe concomitant non‐cardiac disease Pregnancy Recent (<3 months) MI, percutaneous or surgical myocardial revascularization Significant heart valve disease (severe insufficiency or stenosis) Contraindication for oral anticoagulation Mechanical tricuspid valve replacement Unwillingness to participate or lack of availability for follow‐up

AF, atrial fibrillation; CRT, cardiac resynchronization therapy; ICD, implantable cardioverter‐defibrillator; MI, myocardial infarction; NT‐proBNP, N‐terminal pro‐B‐type natriuretic peptide; PM, pacemaker.

Eligible patients will undergo baseline evaluation including clinical history, 12‐lead electrocardiogram, assessment of New York Heart Association (NYHA) class and European Heart Rhythm Association score of AF (EHRA‐AF), echocardiographic examination, assessment of quality of life, 6‐min walk test (6MWT), and blood testing. Quality of life and symptoms will be evaluated with the Kansas City Cardiomyopathy Questionnaire (KCCQ). Subjects fulfilling all inclusion criteria, without meeting any exclusion criteria, will be automatically randomized in a 1:1 ratio to BVP + AVNA or CSP + AVNA. Randomization will be performed automatically according to the previously generated random allocation list. Both groups will be treated identically in all respects except for the intervention being tested. There will be no restrictions on medical therapy adjustments during the study. Optimization of guideline‐directed medical therapy following HF guidelines will be encouraged, but at the discretion of the treating physician.

### Study objectives and endpoints

The CONDUCT‐AF study aims to confirm the non‐inferiority of CSP versus BVP in echocardiographic and clinical outcomes, during a 24‐month follow‐up in HF patients with symptomatic AF and narrow QRS scheduled for AVNA. The study primary endpoint is the LVEF change from baseline to 6 months. Changes in indexed LV end‐diastolic and end‐systolic volumes from baseline to 6 months will be reported as secondary endpoints. These will also include the composite of worsening HF or cardiovascular death and its individual components. Worsening HF was defined as an episode of HF that requires unplanned medical attention with an increase in diuretic dose or intravenous diuretic therapy or HF hospitalization. The total number of HF hospitalizations will be reported. Clinical parameters, including changes in functional NYHA class, NT‐proBNP level, quality of life, and 6MWT distance, will be assessed after 6 months. Additional secondary endpoints are safety endpoints related to procedure success and adverse events. A detailed list of pre‐specified study endpoints is provided in *Table* *2*.

**Table 2 ejhf70013-tbl-0002:** Primary and secondary endpoints of the study

Outcomes	Time frame
Primary outcome measure	
Change in left ventricular ejection fraction	Baseline and 6 M
Secondary outcome measures	
Time to the first occurrence of worsening HF or cardiovascular death	At least 24 M
Time to the first occurrence of worsening HF	At least 24 M
Time to cardiovascular death	At least 24 M
Total number of HF hospitalizations	At least 24 M
Change in indexed LV end‐diastolic and end‐systolic volumes	Baseline and 6 M
Improvement in clinical parameters (NYHA class, EHRA‐AF, KCCQ score)	Baseline and 6 M
Change in the 6‐min walk test	Baseline and 6 M
Laboratory parameters – NT‐proBNP	Baseline and 6 M
Procedural‐related characteristics (total procedure and fluoroscopy time)	Peri‐procedural
Procedure‐associated adverse events	30 days after the procedure
Need for procedural reintervention	At least 24 M
ECG parameters (QRS duration)	Baseline and after the procedure
Pacing parameters (capture threshold, lead impedance)	At least 24 M
Number of detected sustained VT/VF	At least 24 M

ECG, electrocardiogram; EHRA‐AF, European Heart Rhythm Association score of atrial fibrillation; HF, heart failure; KCCQ, Kansas City Cardiomyopathy Questionnaire; LV, left ventricular; M, months; NT‐proBNP, N‐terminal pro‐B‐type natriuretic peptide; NYHA, New York Heart Association; VF, ventricular fibrillation; VT, ventricular tachycardia.

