### Sample size and statistical considerations

The study is designed to test the two‐sided hypothesis, at a type I error level of 0.05, that participants assigned to the CSP group would achieve a non‐inferior improvement of LVEF compared to the participants assigned to the BVP group, with the non‐inferiority margin of 5%. Additionally, an allowable absolute difference of 5% in echo measurement of LVEF with Simpson biplane was set to cover the intraobserver variability. To estimate the sample size and study power, we used the linear mixed model. Although there is an absence of robust estimation from the literature, according to the non‐randomized study, the predicted mean change of LVEF in the population would be +12% in the CSP group and −1% in the BVP group.^24^ According to available data, the maximum standard deviation of measured LVEF in the CSP group was 13% and 15% in the BVP group.^21^, ^23^, ^24^ Therefore, the LVEF change in the CSP group would be distributed in the population as *N* (12, 13^2^) and in the BVP group as *N* (−1, 15^2^). Based on these assumptions, we calculated that the necessary sample size would be 70 participants (35 patients in each group) to achieve a power of 0.9996 and yield a statistically significant result. The dropout rate was assumed at 15% due to study withdrawal or loss to follow‐up. Consequently, the target patient number was set as 82 participants.

Acknowledging limited data available in the literature, we conducted several sample size simulations to address the robustness of our assumptions across a plausible range of ejection fraction responses after both pacing modalities. Even in a more conservative scenario where the CSP group follows a *N* (7, 13^2^) and BVP group a *N* (0, 15^2^) distribution, the calculated power remains above 80%. The ALTERNATIVE‐AF trial showed improvement in LVEF in both pacing modalities with only 5% absolute difference in favour of CSP.^28^ Even in this scenario (CSP mean ejection fraction change: +12%, BVP mean ejection fraction change: +7%), the calculated power would remain >95% to demonstrate the non‐inferiority.

Data management will be performed using the Research Electronic Data Capture – REDCap (Vanderbilt, Nashville, TN, USA) and statistical analyses using the R programming language. The trial will follow an intention‐to‐treat analysis approach.

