### Study limitations

A potential limitation of this study is the small sample size that was calculated to achieve statistically significant results and prove the non‐inferiority of CSP compared to BVP in the primary outcome – change in LVEF. Although our study may provide some insight into hard endpoints, adequately powered, large‐scale randomized clinical trials with long‐term follow‐up will be required to confirm our findings regarding morbidity and mortality. As only patients with reduced LVEF and narrow QRS will be included, the results cannot be extrapolated to other subgroups of patients undergoing AVNA.

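### The stated aim is to confirm non-inferiority in clinical outcomes as well as LVEF, but the only hypothesis, margin and sample size are for LVEF change, and 82 patients cannot support such a claim for clinical events

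*Protocol article*

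**What the plan says.** Two places state the aim. The abstract (Aims) asks whether CSP is non-inferior to BVP "in improving left ventricular ejection fraction (LVEF) and clinical outcomes in heart failure (HF) patients". The section on study objectives and endpoints says that the study aims to confirm non-inferiority "of CSP versus BVP in echocardiographic and clinical outcomes", over 24 months of follow-up.

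The statistical section is narrower. It begins "The study is designed to test the two‐sided hypothesis, at a type I error level of 0.05" and goes on to a non-inferiority hypothesis about LVEF improvement, "with the non‐inferiority margin of 5"%. All its power scenarios concern LVEF change.

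Table 2 makes 6-month LVEF change the primary outcome. Time to worsening heart failure or cardiovascular death, its components and total heart failure hospitalizations are secondary, over at least 24 months. NYHA class, EHRA-AF score, KCCQ, 6-minute walk and NT-proBNP are secondary at 6 months.

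The section on study limitations says that the sample size was calculated for LVEF change. It continues "Although our study may provide some insight into hard endpoints", and then says that larger trials with sufficient power and long follow-up will be needed for morbidity and mortality.

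**The concern.** To confirm non-inferiority is a claim about error control: a stated margin is excluded with a stated confidence. The document sets this up for LVEF change and for nothing else, but the aim extends the claim to clinical outcomes. The limitations section then offers only some insight into the hardest of those outcomes. For clinical events the two statements cannot both stand.

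What is at stake is what the trial may conclude. With few events, the likely result for worsening heart failure or cardiovascular death is a wide interval that includes 1. Set against an aim of confirming clinical non-inferiority, that result could be taken as meeting the aim while remaining compatible with a considerable excess of events under CSP.

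**Working it through.** **1. What the sample size belongs to.** Inputs from the section on sample size and statistical considerations: mean LVEF change +12 (CSP) and −1 (BVP), so a difference of 13; SDs 13 and 15; margin 5; 35 per arm. The two-sided 0.05 is taken as one-sided 0.025 for non-inferiority.

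- SE = √[(13² + 15²)/35] = √(394/35) = 3.355
- Power = Φ[(13 + 5)/3.355 − 1.96] = Φ(3.405) = 0.9997; with the noncentral t it is 0.9996
- Dropout: 70/(1 − 0.15) = 82.4, against 82 stated

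The stated power of 0.9996 and the target of 82 are reproduced from LVEF inputs alone. No clinical outcome enters.

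**2. What a clinical-event claim would need.** The document gives no event rate and no hazard-ratio (HR) margin, so a range of each is assumed. The calculation covers time to first worsening heart failure or cardiovascular death, with 1:1 allocation and a true HR of 1.

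- Events for 80% power: D = 4(1.960 + 0.842)²/(ln margin)² = 31.4/(ln margin)²
- Margin 1.5: 31.4/0.1644 = 191. Margin 2.0: 31.4/0.4805 = 65.3, so 66
- Power with D events: Φ[(√D/2) ln(margin) − 1.96]

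| HR margin | Events for 80% power | Events per enrolled patient (÷ 82) | Power if 20% to 50% have an event (16 to 41 events) | Power if all 82 have an event |
|---|---|---|---|---|
| 1.25 | 631 | 7.7 | 7% to 11% | 17% |
| 1.3 | 457 | 5.6 | 8% to 13% | 22% |
| 1.5 | 191 | 2.3 | 13% to 25% | 45% |
| 2.0 | 66 | 0.80 | 29% to 60% | 88% |

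Each patient contributes at most one first event, so 82 is a ceiling whatever the length of follow-up. It is a generous one, because the plan itself allows for 15% dropout.

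**3. Precision.** SE(ln HR) = 2/√D. With an observed HR of 1:

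- 20% with an event, D = 16.4: exp(±1.96 × 0.494), a 95% interval of 0.38 to 2.6
- 50% with an event, D = 41: exp(±1.96 × 0.312), a 95% interval of 0.54 to 1.8

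The smallest margin with 80% power, exp(2.80 × 2/√D), is 4.0 and 2.4 respectively.

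**4. If CSP is truly better.** With a true HR of 0.7, ln(margin) is replaced by ln(margin/0.7). At 30% with an event (24.6 events), power is 34% at margin 1.3 and 47% at margin 1.5. At 50% it is 51% and 68%. For 80% power at margin 1.5, D = 31.4/(ln(1.5/0.7))² = 31.4/0.581 = 54.05, so 55 events, or 67% of 82 patients.

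**The case against.** The strongest reply is that the article, read whole, already makes the restriction. The hypothesis is tied to LVEF, the objectives section names 6-month LVEF change as primary right after the aim, the clinical events are secondary, and the limitation is disclosed. That is a fair account of the design, and it is why the repair is one of wording. It does not remove the fault. The aim still says the opposite in the two places where a reader looks for it, and the abstract carries no caveat.

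A second reply is that an analysis plan, not shown, may hold clinical margins or declare these endpoints descriptive. This stands in part: the absence of a clinical margin from the article is not itself a fault. But no analysis plan can supply events that 82 patients do not generate, and declaring the endpoints descriptive would contradict the aim as printed.

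Three stronger readings are tempting, and the documents do not support them.

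- A reader might infer that echocardiographic non-inferiority is promised over 24 months although imaging stops at 6. Table 2, Table 3 and the section on echocardiographic examination consistently place the LVEF and LV-volume endpoints at 6 months. The 24 months can be read as the trial's overall follow-up.
- A reader might infer that no part of the clinical aim can be met. The calculation covers time to first event only. Nothing was computed for KCCQ, 6-minute walk, NYHA class, EHRA-AF score or NT-proBNP at 6 months, and total hospitalizations can exceed one per patient.
- A reader might infer that a null result will be reported as non-inferiority. The document nowhere says so, and its limitations section points the other way.

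**Conclusion.** The point holds for the wording of the aim. The abstract and the objectives section state a confirmatory non-inferiority aim for clinical outcomes that the statistical section does not set up and the limitations section partly withdraws.

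For time to worsening heart failure or cardiovascular death with a true HR of 1, 80% power is out of reach at margins up to 1.5 even if every patient had an event. At 2.0 it requires about 80% of patients to have one. The margins, the event rates and the true HR are assumptions. A true benefit of CSP would ease the requirement, but power stays below 80% at margins of 1.3 and 1.5 for a true HR of 0.7 with up to half of patients having an event. The conclusion that clinical events will be imprecisely estimated does not depend on where in the assumed range the truth lies, and it agrees with the document's own limitation.

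**What to change.** In the abstract (Aims) and in the section on study objectives and endpoints, restrict the confirmatory non-inferiority aim to LVEF change from baseline to 6 months. In the same places, state that the clinical endpoints are secondary and are reported as effect estimates with 95% confidence intervals, and that no non-inferiority conclusion will be drawn from a non-significant difference in clinical events.

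Nothing changes in sample size, visits, imaging or data collection. The cost is a narrower claim, and it brings the aim into line with the limitations section. It can be made before the primary analysis expected in 2026 and the secondary reporting expected by the end of 2027.
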